## Study assessments and procedures

### Dose titration

A single-arm dose titration trial (Table 1). Sample size: minimum 15 patients (3 patients per dose level) – maximum 30 (6 patients per dose level) patients.

Table 1. Dose escalation of 5-FU 24-hour EPIC for each titration level and concomitant treatment where irinotecan is also an investigational drug (the other drugs are non-investigational and given to both groups in the randomized part of the trial).

| Level | Non-investigational  Oxaliplatin | **Investigational**  **Irinotecan** | **Investigational**  **5-FU**  **24-hour EPIC** | Non-investigational  5-FU  bolus | Non-investigational  Calcium folinate |
| --- | --- | --- | --- | --- | --- |
| -1 | 360 mg/m^2^ | **360 mg/m^2^** | **250 mg/m^2^** | 400 mg/m^2^ | 60mg/m^2^ |
| 0 | 360 mg/m^2^ | **360 mg/m^2^** | **400 mg/m^2^** | 400 mg/m^2^ | 60mg/m^2^ |
| 1 | 360 mg/m^2^ | **360 mg/m^2^** | **550 mg/m^2^** | 400 mg/m^2^ | 60mg/m^2^ |
| 2 | 360 mg/m^2^ | **360 mg/m^2^** | **700 mg/m^2^** | 400 mg/m^2^ | 60mg/m^2^ |
| 3 | 360 mg/m^2^ | **360 mg/m^2^** | **850 mg/m^2^** | 400 mg/m^2^ | 60mg/m^2^ |

Endpoint is Clavien-Dindo morbidity classification 3b-5 (Table 2). All patients will be reviewed at each of the dose levels by the DMC prior to allowing the next group of patients to advance to the following level. The toxicity follow-up is 30 days if no incidents occur. If the postoperative rehabilitation is slower or incidents occur, the follow-up period may be extended to by the site Principal Investigator or Co-investigator.

If none or one of the first three patients at a dose level has a grade 3b-4b the DMC will review the data and permit the start of the next level. If more than one patient experiences a grade 3b-4b another three patients will be included at the same dose level before the DMC will review the data. A frequency of 3b-4b morbidity in ≤1 of 3 or ≤2 of 6 patients may result in a recommendation by the DMC to proceed to the next dose level. A higher frequency of grade 3b-4b means the maximum tolerated dose (MTD) has been passed, and the dosage used in the efficacy study will be the nearest underlying dose level. Any grade 5 event pauses all inclusion for review. Depending on cause, the trial may continue after DMC review.

Table 2. Clavien-Dindo classification.

| Grades | Definition |
| --- | --- |
| Grade 1 | Any deviation from the normal postoperative course without the need for pharmacological treatment or surgical, endoscopic and radiological interventions Allowed therapeutic regimens are drugs as antiemetics, antipyretics, analgesics, diuretics and electrolytes and physiotherapy. This grade also includes wound infections opened at the bedside. |
| Grade 2 | Requiring pharmacological treatment with drugs other than such allowed for grade 1 complications. Blood transfusions and total parenteral nutrition are also included. |
| Grade 3 | Requiring surgical, endoscopic or radiological intervention |
| -3a | Intervention not under general anaesthesia |
| -3b | Intervention under general anaesthesia |
| Grade 4 | Life-threatening complication (including CNS complications) requiring IC/ICU-management |
| -4a | Single organ dysfunction (including dialysis) |
| -4b | Multi-organ dysfunction |
| Grade 5 | Death of a patient |

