| Criteria for evaluation:  Safety: Safety will be assessed by the Clavien-Dindo classification and reporting of Adverse Events.  The maximum tolerated dose of 5-FU will be determined by giving the first 15-30 patients escalating doses of 5-FU. The morbidity of each dose level of 5-FU 24-hour EPIC will be evaluated by the Data Monitoring Committee 30 days post-treatment. A dose level with ≤1/3 or ≤2/6 with 3b-4 Clavien-Dindo morbidity may proceed to the next dose level. Following the dose titration study, all patients will receive the maximum dose of 5-FU. An interim safety evaluation will be performed after the first 140 patients have been randomized and treated with HIPEC or HIPEC in combination with EPIC. The Clavien-Dindo grade 3-5 morbidity is expected to be approximately 0.35 (35%). If the experimental arm’s 95% CI falls within 0.4 or below, the study will be allowed to continue.  Efficacy: Recurrence free survival (RFS) is determined at 12-months post treatment through the HIPEC registry. Postoperative complications rates with-in 30 days, 5-year overall survival and RFS are further determined through the HIPEC registry and quality of life is assessed by questionnaires through the QoL registry. | | |
| **Dosage of Investigational Products:**  The maximum tolerated dose (MTD) of 5-FU will be determined by giving the first 15-30 patients escalating doses of 5-FU. The morbidity of each dose level of 5-FU 24-hour EPIC will be evaluated by the Data Monitoring Committee within 30 days post-treatment. A dose level with ≤1 of 3 patients or ≤2of 6 patients (extended group size) with 3b-5 morbidity may proceed to the next dose level. If the frequency of 3b-5 morbidity is higher, MTD has been passed and the dose of 5-FU in the efficacy study will be the next lower dose level. If MTD is not reached the highest dose level of 5-FU (850 mg/m^2^) will be used. | | |
| Statistical methods:  Recurrence free and overall survival of the two arms will be compared using the parameters: treatment arm, age, PCI, CC score, use of systemic perioperative chemotherapy (neoadjuvant and/or adjuvant), concomitant liver metastases resection, colon or rectal primary tumor, and lymph-node metastasized primary tumor.  QoL will be analyzed by comparing the answers to questions 29 and 30 in QLQ-C30 by Mann-Whitney U test and Freidman’s repeated measures ANOVA test. Specifically, differences between the sexes will be investigated.  Statistical significance will be set at p=0.05. | | |

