## Safety parameters

Clavien-Dindo morbidity was chosen as the most relevant morbidity grading system. The oxaliplatin/irinotecan/5-FU combination for systemic chemotherapy is already well known in oncology under different acronyms (FOLFIRINOX, FOLFOXIRI). As such, the toxicity profile of this triple combination is already known. This study will assess whether it is compatible with a surgical intervention using the Clavien-Dindo surgical classification. However, some basic blood chemistry as specified in section 8.3 (extended part of the HIPEC registry employed only for the dose titration study) will be added to verify the rate of non-surgical toxicity. As the 24-hour EPIC has not previously been dose-titrated, we will titrate to a maximum of 850 mg/m^2^. Clavien-Dindo 3a was excluded as a stopping factor due to its common use postoperatively after CRS+HIPEC for draining fluid collections (most commonly pleural effusion often caused by diaphragmatic stripping of the peritoneum and is dependent upon the extent of the stripping).

All patients will be reviewed at each of the dose levels by the DMC prior to advancing to the next level. It is Clavien-Dindo grade 3b-5 morbidity that will be reviewed. A dose level with ≤1/3 or ≤2/6 with 3b-4b morbidity may proceed to the next dose level. Max tolerated 3b-4b morbidity is 33 %. Statistical testing is unnecessary. All grade 5, leading to death, will halt study progression. A formal review with the DMC will ensue before the study will be allowed to continue or be terminated permanently. Two grade 5 events may be cause for study termination after DMC review.

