## Statistical analysis

### Statistical methods

#### Dose titration study

The dose titration study will include 3 patients at each dose level, with a possibility to include 3 more patients if more than 1 patient experiences morbidity grade 3b-5 (3 + 3 design). In order to complete all 5 dose levels 15-30 patients will be needed depending on how often the second three patients are needed at each dose level. The toxicity follow-up is 30 days if no incidents occur. If the postoperative rehabilitation is slower or an incident occurs, the follow-up period may be extended by the site Principal Investigator or Co-investigator. Circa 3-4 colorectal cancer patients are treated with CRS+HIPEC each week in Sweden. Dose titration can be completed within 15-30 weeks.

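### Phase I escalation rules: three more patients are required after 3 of 3 events although the level has already failed, the limit is stated both with and without deaths, and 12.1 puts DMC review inside the 30-day window that 8.1 makes it follow

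*Protocol*

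**What the plan says.** **Expansion.** Section 8.2.1 treats three patients at a dose level and then states: "If more than one patient experiences a grade 3b-4b another three patients will be included at the same dose level before the DMC will review". Section 13.2.1 describes the same step as optional and with a different grade range: "with a possibility to include 3 more patients if more than 1 patient experiences morbidity grade 3b-5".

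**Decision limit.** Section 8.2.1 defines the outcome as "Endpoint is Clavien-Dindo morbidity classification 3b-5", but its limit reads: "A frequency of 3b-4b morbidity in ≤1 of 3 or ≤2 of 6 patients may result in a recommendation by the DMC to proceed". Anything higher means that the MTD has been exceeded, and phase III takes the next lower dose. Section 12.5 has the same split. It says "It is Clavien-Dindo grade 3b-5 morbidity that will be reviewed" and then "A dose level with ≤1/3 or ≤2/6 with 3b-4b morbidity may proceed to the next dose level". The synopsis row on criteria for evaluation has "A dose level with ≤1/3 or ≤2/6 with 3b-4 Clavien-Dindo morbidity may proceed to the next dose level", while the synopsis row on dosage applies the same fractions to grade 3b-5.

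**Deaths.** Under 8.2.1 any grade 5 event stops inclusion until the DMC has looked at it, and the trial may then resume. Section 12.5 adds: "Two grade 5 events may be cause for study termination after DMC review".

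**Timing.** Section 8.1 has each group followed for 30 days before the DMC decides on the next dose. Section 12.1 places the formal DMC assessment no later than 30 days after the last operation at the level. The synopsis dosage row also speaks of evaluation within 30 days; the criteria row says 30 days.

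**The concern.** The MTD is the phase I primary endpoint and fixes the phase III dose, so a site and the DMC need one rule that gives one answer. As written, three situations have no clean answer.

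- After 3 of 3 events, 8.2.1 calls for three more patients at that dose and places the DMC's review after them, although the level can no longer meet its own limit. Those patients would carry risk for no information that affects the decision.
- After a death, and once the DMC has let the trial resume, the tally for that level depends on which sentence is applied.
- A DMC following 12.1 could clear a level before the last patient's 30-day toxicity window has closed.

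**Working it through.** **Inputs.** Five dose levels, three or six patients each, limits ≤1/3 and ≤2/6 (8.2.1); maximum tolerated 3b-4b morbidity 33% (12.5). The protocol gives no expected event rate per dose level, so the true rates p below are assumptions. The protocol's own figures reproduce: 5 × 3 = 15 and 5 × 6 = 30 patients, and 1/3 = 2/6 = 33%.

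**1. Expansion after 3 of 3.** A six-patient cohort starts from 2 or 3 events and adds 0 to 3, which gives eight paths. Only 2 + 0 = 2 meets ≤2/6. From 3 of 3 the smallest total is 3/6 = 50%.

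- P(3 of 3) = p³
- P(level passes) = (1−p)³ + 3p(1−p)² + 3p²(1−p)·(1−p)³
- Expected patients spared per level by not expanding 3 of 3 = 3p³

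| Assumed p | P(3 of 3) | Patients spared per level | P(level passes), either rule |
|---|---|---|---|
| 20% | 0.8% | 0.02 | 94.5% |
| 25% | 1.6% | 0.05 | 90.3% |
| 33% (1/3) | 3.7% | 0.11 | 80.7% |
| 40% | 6.4% | 0.19 | 71.0% |
| 50% | 12.5% | 0.38 | 54.7% |

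The pass probability is the same with and without the expansion, because 3 of 3 fails either way. The share of all expansions that follow 3 of 3 is p³ / [3p²(1−p) + p³] = p/(3−2p): 14% at 1/3, 18% at 40% and 25% at 50%.

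**2. Does a death count?** Suppose that of three patients one survives a grade 4 event, one dies without any earlier grade 3b-4b event, and one has neither. Counting 3b-4b gives 1/3, so the level may proceed. Counting 3b-5 gives 2/3, so the cohort is expanded.

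An upper bound on how often the two tallies disagree on pass or fail follows if (a) death and a 3b-4b event are taken as mutually exclusive within a patient and (b) the trial continues after every death. With 3b-4b rate q and death rate d, a level that passes on 3b-5 always passes on 3b-4b, so disagreement = P(pass at q) − P(pass at q + d). For example, q = 20% and d = 5%: 0.945 − 0.903 = 0.042.

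| q | d = 1% | d = 2% | d = 5% |
|---|---|---|---|
| 20% | 0.7% | 1.5% | 4.2% |
| 25% | 1.0% | 2.0% | 5.4% |
| 33% (1/3) | 1.4% | 2.7% | 7.1% |

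The death rates are assumptions. The 5% is the in-hospital mortality ceiling that 13.2.1 sets for the phase III interim analysis, not an expected rate.

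**3. Timing.** Let day 0 be the last operation at a level. Section 12.1 allows assessment on any day up to day 30. Section 8.1 requires 30 days of follow-up first. Only day 30 itself satisfies both. If follow-up is extended, as 8.2.1 and 13.2.1 allow, and the review is meant to wait for it, no day does.

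**The case against.** **Little is at stake in part 1.** At or below the tolerated 33%, the change spares at most 0.11 expected patients per level. The next sentences of 8.2.1 already say that a frequency above the limits means the MTD is passed, 13.2.1 makes expansion optional, and serious events reach the DMC chair within 24 hours, who may pause the trial (12.1). All of this reduces the harm. It does not remove the instruction: the expansion sentence is mandatory, covers 3 of 3 and precedes the formal review, while the pause is discretionary. A reader might infer that this expansion could let a toxic dose through. It cannot, since no path from 3 of 3 meets the limit.

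**Part 2 may be a two-track rule.** Sections 8.2.1 and 12.5 can be read as tallying non-fatal events against 33% and sending every death to separate review. That is a fair reading of those two sections, and it rules out the inference that deaths are ignored. It does not fit the synopsis dosage row or the trigger in 13.2.1, which both count 3b-5, and no section says how a death enters the tally after a restart. Nor are the percentages in the second table error rates. A patient who needed reoperation or intensive care before dying may already count as 3b-4b, every death pauses inclusion, two may end the study, and no level advances without the DMC.

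**Part 3 rests mainly on one sentence.** Section 8.1 and the synopsis criteria row point to a 30-day window, and the dosage row may simply describe 30-day morbidity. The conflict in 12.1 remains. A reader might also count the 15-week lower estimate for titration as evidence of early review, but it is a feasibility estimate, and 13.3 allows six months.

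**Conclusion.** The point holds in three parts, each moderate in consequence and worth correcting.

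1. The futile expansion follows from the text of 8.2.1 without any assumption. Its frequency rests on assumed event rates: 3.7% of levels at 33% and 12.5% at 50%. The harm is needless exposure of three patients, not a wrong dose. Expansion after exactly 2 of 3 is coherent and is not criticised.
2. The limit is stated in two incompatible ways. The gap that remains is narrow: a death with no earlier counted 3b-4b event, in a trial that the DMC has allowed to resume. Disagreement in 0.7% to 7.1% of levels is an upper bound under the two simplifications stated and assumed death rates of 1% to 5%.
3. Section 12.1 contradicts 8.1 and, taken literally, permits review before the toxicity window closes. The documents do not show that the DMC intends to review early.

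The 24-hour alert, the mandatory pause for any death and the DMC's freedom not to proceed limit the damage. They do not say which rule governs.

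**What to change.** - **8.2.1 and 13.2.1:** expand to six only when exactly 2 of the first 3 patients have an event. Declare the MTD passed at 3 of 3, or as soon as a third event is known in an expanded cohort. Use the same wording in both sections.
- **Synopsis criteria row, 8.2.1 and 12.5:** count grade 3b-5 in every decision limit, matching the stated endpoint. Keep the pause for any death and the two-death provision as separate safeguards.
- **12.1 and synopsis dosage row:** state that the DMC reviews a level after the last patient has completed the 30-day, or extended, follow-up.

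The cost is a few sentences. Three patients are spared whenever 3 of 3 occurs. Counting deaths can occasionally trigger an expansion of three patients that the 3b-4b tally would not, within the planned maximum of 30. The timing change adds up to about 30 days per level against the literal wording of 12.1 and nothing against 8.1.

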### Efficacy study

Figure 2: Flowchart for the efficacy study

| All colorectal cancers with peritoneal metastases | | | | |
| --- | --- | --- | --- | --- |
| ↓  Randomization intraoperatively  ↙ ↘ | | | | |
| **A: Standard HIPEC**  **(70 patients)**   1. Oxaliplatin  - 460 mg/m^2^ (HIPEC)  1. 5-fluorouracil  - 400 mg/m^2^ IV bolus (Intraop)  1. Calcium folinate  - 60 mg/m^2^ IV (Intraop) | |  | **B:** **Intensified HIPEC+EPIC**  **(70 patients)**   1. Oxaliplatin    - 360 mg/m^2^ (HIPEC) 2. Irinotecan    - 360 mg/m^2^ (HIPEC) 3. 5-FU Bolus    - 400 mg/m^2^ IV (Intraop) 4. Calcium folinate 5. 60 mg/m^2^ IV (Intraop) 6. 5-FU 24-hr EPIC  - According to the dose titration study | |
|  | |  | Prophylactic G-CSF postop day 4-8 | |
| ↓ |  | | | ↓ |
| Interim safety evaluation:  Grade 3-5 Clavien-Dindo morbidity comparison | | | | |
| ↓ | | | | |
| **A: Standard HIPEC**  **(163 patients)** | |  | **B:** **Intensified HIPEC+EPIC**  **(163 patients)** | |
| ↓ | |  | ↓ | |
| Primary endpoint:   - 12-month RFS   Secondary endpoints:   - Overall survival and RFS up to 5 years: Through the HIPEC registry - QoL: Through the QoL registry - Morbidity: Through the HIPEC registry | | | | |

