### Interim safety analysis of the Efficacy study

After randomization, the Clavien-Dindo grade 3a-4b morbidity is expected to be approximately 25-35% when treating patients with the dose of 5-FU determined from the dose titration study. During the interim analysis of the efficacy part of the trial, the DMC will use the morbidity rate of the standard arm and compare it to the experimental arm. If all Clavien-Dindo grade 3-4 complications resolve in-hospital and occur at a maximum rate of 40%, the trial will pass the interim review. If complications lead to permanent sequelae or the rate is higher than 40% a detailed review by the safety committee will ensue prior to letting the efficacy study continue. Comparison with the standard arm will assist in determining the risk/possible benefit ratio. In particular, if the mortality rate is increased, it will be grounds for discontinuing the trial. The trial may be allowed to continue despite increased morbidity if the mortality rates are the same and if the morbidity is of a temporary nature, not leading to permanent functional loss. The decision will be made by the DMC. If necessary, dose reduction may be considered in order to continue and complete the efficacy study.

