#### Interim analysis

The Clavien-Dindo grade 3-4 morbidity is expected to be approximately 0.35 (35%) for patients receiving the maximum dose of 5-FU. Allowing for a small increase in morbidity to 0.40 and an accepted 95% confidence interval width of 0.15, at least 66 patients are needed in the experimental arm to determine whether the arm deviates from the expected morbidity rate. The total sample size will be 140 (70 per arm) for an interim trial safety evaluation (circa 50% of trial included). If the Clavien-Dindo grade 3-4 morbidity falls outside of the 40% mark, then a Fisher’s exact test comparison between the standard and experimental arm will be performed together with a mortality comparison. Concerning in-hospital mortality, a maximum rate of 5% will be set. This planned interim safety evaluation will be unpublished. If the morbidity is increased beyond the set mortality limit or the increase is of a more serious nature, the trial will either be discontinued or alternatively, depending on the character of the complications, a lower dose level may be employed.

The overall survival and recurrence free survival will be reviewed during this interim safety evaluation to see if a primary endpoint of overall survival is attainable with increased cohort size instead of 12-month RFS. If attainable depending on inclusion rate, the endpoint will be changed, and a new sample size calculation will be performed. Likewise, a choice between 3 or 5 year follow-up will be made. Alternatively, trial futility will be determined if no differences at all are forthcoming even in the RFS setting. In this case, the trial will close prematurely. A decision to close the trial is made by the sponsor in conjunction with site investigators.

Possible changes of dose level, endpoint, sample size calculation or other substantial changes will be submitted to the MPA and ERA as an amendment to the protocol.

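### The phase III interim safety gate counts Clavien-Dindo grade 3-5 in the synopsis and Figure 2 but grade 3-4 in sections 12.5.1 and 13.2.1, with one 40% limit

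*Protocol*

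**What the plan says.** Four places in the protocol describe the same interim review of 140 patients (70 per arm).

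- **Synopsis, Criteria for evaluation:** "The Clavien-Dindo grade 3-5 morbidity is expected to be approximately 0.35 (35"%). The trial continues if the experimental arm's "95% CI falls within 0.4 or below, the study will be allowed to continue".
- **Section 8.2.2, Figure 2:** "Grade 3-5 Clavien-Dindo morbidity comparison". No expected rate and no threshold are given.
- **Section 12.5.1:** "the Clavien-Dindo grade 3a-4b morbidity is expected to be approximately 25-35"%. The pass rule then reads: "If all Clavien-Dindo grade 3-4 complications resolve in-hospital and occur at a maximum rate of 40%, the trial will pass the interim review". A higher rate, or permanent sequelae, leads to a detailed review. Increased mortality is named separately as grounds for discontinuing.
- **Section 13.2.1, Interim analysis:** grade 3-4 is expected at 35%. The trigger begins "If the Clavien-Dindo grade 3-4 morbidity falls outside of the 40% mark", and then a Fisher's exact test between arms and a mortality comparison follow. Separately: "Concerning in-hospital mortality, a maximum rate of 5% will be set".

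Table 2 defines grade 5 as death.

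**The concern.** Section 5.4 explains that this interim review takes the place of a phase II trial, so its event should be fixed. Two events that differ by exactly the fatal cases are held against one limit, with nearly the same expected rate (35% in the synopsis and 13.2.1, 25-35% in 12.5.1). For an arm near the limit, whether the Data Monitoring Committee (DMC) passes it or opens a detailed review can depend on which section it follows.

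The direction of the difference also matters. Under the grade 3-4 wording, a patient whose worst grade is 5 need not appear in the numerator, although the patient remains in the denominator. The trigger in 13.2.1 for comparing mortality between arms is itself set on that count.

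**Working it through.** **Inputs.** 70 patients per arm, limit 40% and in-hospital mortality limit 5% (13.2.1; the 40% also in 12.5.1 and the synopsis); grade 5 = death (Table 2). Two assumptions are mine: each patient is counted once at the worst grade, and the true death rate is 1, 2, 3 or 5%.

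**The plan's own interim size.** Section 13.2.1 gives at least 66 patients for a 95% confidence interval width of 0.15. With n = 1.96² p(1−p)/h², a full width of 0.15 (h = 0.075) needs 156 at p = 0.35 and 164 at p = 0.40. Read as a half-width (h = 0.15), it needs 39 and 41. Neither reading gives 66. That is a separate matter and does not affect this point, which uses the 70 per arm as stated.

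**Counts at the limits.** 0.40 × 70 = 28 events. 0.05 × 70 = 3.5, so 3 deaths (3/70 = 4.3%) stay under the mortality limit and 4 (4/70 = 5.7%) exceed it.

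**Same arm, two counts.** Take 28 patients at worst grade 3-4 and 3 deaths.
- Grade 3-4: 28/70 = 40.0%, at the limit.
- Grade 3-5: 31/70 = 44.3%, above it.

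The difference of 4.3 points is most of the 5-point allowance between 35% and 40%.

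**Morbidity criterion alone.** At a true grade 3-5 rate of 40%, P(at most 28/70) is 0.55 on the grade 3-5 count. On the grade 3-4 count the event rate is 0.40 minus the death rate, which gives 0.62, 0.68, 0.74 and 0.84 for death rates of 1, 2, 3 and 5%.

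**Morbidity and mortality limits together.** Let q be the true grade 3-5 rate, m the death rate and p = q − m. With K deaths among 70 patients (binomial, rate m), the number X at worst grade 3-4 among the other 70 − K is binomial with rate p/(1 − m). Then:
- Grade 3-4 count: Σ over k = 0..3 of P(K = k) · P(X ≤ 28 | k)
- Grade 3-5 count: Σ over k = 0..3 of P(K = k) · P(X ≤ 28 − k | k)

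For q = 0.40:

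| Assumed death rate | Pass, grade 3-4 | Pass, grade 3-5 | Difference |
|---|---|---|---|
| 1% | 0.615 | 0.550 | 0.065 |
| 2% | 0.642 | 0.532 | 0.110 |
| 3% | 0.613 | 0.488 | 0.125 |
| 5% | 0.432 | 0.340 | 0.092 |

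At q = 0.45 with 5% deaths the pair is 0.264 and 0.159.

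Both columns use the observed-rate rule of 12.5.1, so that only the event definition differs. The synopsis instead holds the confidence interval against 0.40. With 70 patients that allows only 19 events (Wilson or Clopper-Pearson) or 20 (Wald), so both 28 and 31 events would fail it. That mismatch is separate.

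**The case against.** A reader might infer that more deaths make the interim review easier to pass. The documents do not support this for the review as a whole. Section 13.2.1 caps in-hospital mortality at 5%, section 12.5.1 makes increased mortality grounds for discontinuing, and overall survival is also reviewed at this interim. The table shows it: as the assumed death rate rises from 1 to 5%, the joint pass probability on the grade 3-4 count is roughly flat and then falls to 0.432. Only the morbidity criterion taken alone becomes easier.

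Other points on that side also stand.
- The protocol nowhere says that each patient is counted once at the worst grade. Adverse events are recorded on one form each (section 12.6), so a grade 4 complication before death could still be counted.
- Section 12.5.1 also requires every grade 3-4 complication to have resolved before discharge. A complication that ended in death did not resolve on a natural reading, so an arm with such deaths may already need detailed review there. The 28-plus-3 example is cleanest against the 40% mark in 13.2.1.
- Figure 2 states no threshold, so 44.3% breaches nothing in Figure 2 itself.
- Exceeding 40% does not stop the trial. It opens a detailed review (12.5.1) or a between-arm comparison (13.2.1).

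These points limit the consequence but do not remove the contradiction. The safeguards also leave gaps. The 5% limit covers in-hospital deaths only, so a death after discharge falls outside it and outside the grade 3-4 count. The mortality criterion in 12.5.1 has no figure. Section 13.2.1 states its between-arm mortality comparison only for the case where grade 3-4 morbidity has passed 40%.

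**Conclusion.** The point holds as an internal inconsistency: one interim gate, two events, and one 40% limit shared by the synopsis, 12.5.1 and 13.2.1. The size is bounded. Up to 3 in-hospital deaths in 70 can lie outside the morbidity count without reaching the mortality limit. At a true grade 3-5 rate of 40%, the choice of event then moves the chance of passing both limits by 0.065 to 0.125.

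These figures rest on worst-grade counting, on the assumed death rates, on all deaths being in hospital, and on an observed-rate limit of 28/70. They leave out the in-hospital resolution condition and the DMC's discretion, so they describe the two numerical limits and not the full decision. The inconsistency should be corrected, but it does not show that the trial lacks protection against excess mortality.

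**What to change.** Reconcile the synopsis, Figure 2, section 12.5.1 and section 13.2.1 to one event, counted per patient: the number of patients whose worst grade meets the definition, over all patients treated in the arm. Word the definition so that a fatal outcome cannot lower the counted rate. State the counting rule explicitly. Attach the expected rate and the limiting rate to that event only, and resolve the 35% against the 25-35% in the same edit. Keep mortality as a separate criterion alongside it.

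The cost is wording in a few places, with no change to sample size or data collection. The downside is that, if deaths are included, the counted rate becomes slightly less favourable, so the sponsor should confirm that the expected and limiting rates were meant for the event finally chosen.
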